## Storage, dispensing and packaging of OK432

OK432 will be imported from Japan by Pharmaceutical Solutions Ltd, a UK-based pharmaceutical import agency that accesses unlicensed medications for clinical and research use. Batch assurance, and QP release will be undertaken prior to use in the trial. Pharmaceutical Solutions Ltd will provide full batch traceability in accordance with Good Manufacturing Practice (GMP) and Good Distribution Practice (GDP) guidelines. Batch labelling of IMP is not required.

OK432 will be delivered directly to pharmacies at the collaborating centres. OK432 requires refrigerated storage at a temperature between 2°C and 8°C. In this environment it has a shelf-life of 12 months.

Each course of trial treatment will be pre-prepared in a trial pack (consisting of the appropriate dose of IMP and 50ml of normal saline to enable administration) and dispensed by pharmacy staff to the clinic on the date of intervention visit. Labelling of trial packs will be undertaken at site pharmacies by a clinical trial pharmacist or appropriate delegate, in accordance with TSP05 ‘pharmacy dispensing’. OK432 will be dispensed in sealed boxes (1 box for 5KE dose, 2 boxes for 10KE dose) as produced by the manufacturer, and certified by the QP. Labelling of individual vials will not be undertaken as to do so would obscure the original labelling, and prevent safe reconstitution.

OK432 will be reconstituted in clinic by the trial investigator. The product will be dispensed open-label in its original packaging, with an additional label stating it is an investigational medicinal product (IMP). Pharmacy storage and dispensing of the IMP will adhere to Trial Specific Procedure 5 (TSP05).

## Storage, dispensing and packaging of BCG

BCG will be procured through the usual pharmacy procurement pathways at each centre. BCG requires refrigerated storage at a temperature between 2°C and 8°C, protected from light. In this environment it has a shelf-life of 12 months.

Each course of trial treatment will be pre-prepared in a trial numbered pack and dispensed by pharmacy staff to the clinic on the date of intervention visit. BCG will be dispensed as produced by the manufacturer to be reconstituted in clinic by the trial investigator. The product will be dispensed open-label in its original packaging, with an additional label stating it is an IMP. Pharmacy storage and dispensing of the IMP will adhere to Trial Specific Procedure 5 (TSP05).

## Accountability & unused drugs

Compliance will be audited by completion of electronic case report forms (eCRF) for every administration of OK432/BCG. All used, partially used or unused treatments will be destroyed at study site. The IMP inventory form will be used by the pharmacists to document destroyed IMP.

# NON-TRIAL TREATMENTS

## Usual care

All patients should have been discussed, and had their diagnosis ratified at MDT. Patients should have been referred to their local oncologist for discussion and consideration of chemotherapy and other oncological treatments in the usual manner. Treatment decisions regarding the ongoing clinical care of all participants remain with the primary physician or treating team.

Routine clinical review will take place in the respiratory clinic. The frequency of clinical review will depend on patient choice, severity of symptoms and clinical discretion. Participants who require clinical review more frequently than specified in the TILT schedule of visits will have an eCRF completed for every additional visit.

All attempts should be made to co-ordinate trial follow-up and routine follow-up appointments. Patients should be given the contact details for a mesothelioma specialist nurse at the earliest opportunity.

## Indwelling pleural catheters

### 8.2.1 IPC insertion

An IPC can be inserted by any appropriately trained clinician, including respiratory physicians, thoracic surgeons or member of the research team. The decision to insert an IPC is down to the discretion of the treating clinician.

To be eligible for TILT, participants who do not have an IPC in situ must be willing to have one inserted and must have a pleural effusion of sufficient size and no contra-indications to insertion. These participants should have an IPC inserted as soon after baseline assessment as possible. Participants with a recently inserted IPC should wait at least 14 days before receiving OK432/BCG, if applicable.

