## Exclusion criteria

To be eligible for TILT, participants must have none of the following exclusion criteria:

- No IPC in situ, and has contra-indication to IPC insertion
- Trapped lung with <50% pleural apposition on x-ray
- Moderately heavy or heavily loculated pleural effusion
- Known immunodeficiency or immuno-suppressive medication
- Intercurrent infection (pleural or elsewhere) or clinical signs of sepsis (treatment should be deferred for 7-14 days)
- Active tuberculosis
- Known sensitivity or allergy to OK432, BCG or penicillin
- Previous treatment with immunotherapy
- Recent (<2 weeks) thoracic surgery or invasive pleural intervention (excluding diagnostic/ therapeutic pleural aspiration)
- Currently enrolled in any other interventional clinical trial
- Brain metastases or CNS involvement of MPM
- Pregnancy or lactation, current or planned during the study period
- Age <18
- Any other factor that, in the opinion of the Chief Investigator, would mean participation in the study would be contraindicated

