## Random selection

Participants who meet the eligibility criteria will be identified at scheduled assessment visits during their follow up in ASSESS-meso (TILT screening visit). By capturing data on all potentially eligible participants, the ASSESS-meso database will also function as a screening log, recording data on patients who decline to join TILT, and documenting their reasons for non-participation.

12 eligible participants will be identified and randomly allocated to receive either OK432 or BCG or to remain in ASSESS-meso as a control. Random selection will occur at Week 0. Randomisation will be undertaken by a centralised, concealed, computerised randomisation service, stratified by WHO/ECOG performance status on the day of randomisation, following drainage of (0 vs ≥1) and tumour sub-type (epithelioid/cytological diagnosis versus non-epithelioid). Screening and randomisation are designated ASSESS-meso related activities.

Participants will be unaware that random selection is taking place. Participants who are selected to receive either OK432 or BCG will be informed, provided with a participant information sheet and given time to consider participation, before being invited to join the trial. Participants who are not selected will continue observational follow up in ASSESS-meso. This process is acceptable to ethics committees, as to be eligible for TILT, participants in ASSESS-meso must have already given their consent to undergo randomisation for future trials.

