# TRIAL FOLLOW UP ASSESSMENTS

## Trial visits

As well as an initial screening visit at Week 0, participants will attend 3 trial assessment visits within the subsequent 12 weeks, with participants in the intervention arm returning for two additional visits; one to receive OK432/BCG within 14 days of randomisation (i.e. days 0-14) and a follow-up safety visit on day 3 post-IMP administration. Trial visits will take place at 3 weeks, 6 weeks and 12 weeks post-randomisation.

Participants who receive an IMP will also be contacted by telephone by a member of the trial team, daily for up to 5 days after IMP administration, to check on their well-being. Trial visits must occur as scheduled +/- 3 days, with the exception of the 3 day post intervention visit which must occur on day 3. Trial procedures and assessments for each visit are detailed in section 9.7. The trial flowchart is shown in section 2.4.

Having completed the 12 week trial period, participants will return to clinical follow up as part of the ASSESS-meso. They will participate in ongoing data collection in accordance with the ASSESS-meso protocol which will continue until death, loss to follow up or withdrawal from ASSESS-meso.

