## End of trial (EoT)

Trial recruitment will cease in November 2019, regardless of the number of participants enrolled. EoT date, therefore, will be 12 weeks after enrolment of the 12^th^ trial patient or 12 weeks after the recruitment window closes, whichever happens first. At EoT, participants will return to clinical follow up within ASSESS-meso, which will continue until death, loss to follow up or withdrawal from the study. Data from ASSESS-meso will be used to evaluate overall survival at EoT.

|  |  | **Screening**  **Week 0*** | **Intervention**  **Day 0-14** | **3 days post-intervention**  **(Week 3)** | **Week 6** | **Week 12** |
| --- | --- | --- | --- | --- | --- | --- |
| **Clinical assessment** | Assessment of eligibility | X | **X** |  |  |  |
|  | History of pleural interventions | X |  | X | X | X |
|  | Previous oncological treatment | X |  |  |  |  |
|  | Medication history | X | **X** | X | X | X |
|  | WHO/ECOG performance status | X | **X** | X |  |  |
|  | Vital signs, pulse oximetry | X | **X** |  |  |  |
|  | Physical examination | X |  |  |  |  |
|  | Insertion of IPC (if not already in situ) | X |  |  |  |  |
|  | Pleural fluid drainage diary review | X |  | X | X | X |
|  | Documentation of AEs |  | **X** |  | X | X |
| **Blood tests** | Screening blood tests (HIV screen, hepatitis screen, immunoglobulins, random glucose, thyroid function tests) | X |  |  |  |  |
|  | Pregnancy test  (if female <55 yrs) | X |  |  |  |  |
|  | Coagulation panel | X |  |  |  |  |
|  | Trial blood tests (Full blood count, urea & electrolytes, liver function tests, C reactive protein) | X | **X** | X | X | X |
|  | Serum mesothelin | X |  | X | X | X |
|  | Pleural fluid sampling and storage | X | **X** | X | X | X |
|  | Mantoux test (if logistically possible, BCG arm only) | X |  |  |  | X |
| **Randomisation & intervention** | Random selection | X |  |  |  |  |
|  | Informed consent for TILT |  | **X** |  |  |  |
|  | Administration of OK432/BCG |  | **X** |  |  |  |
| **PROMS** | Breathlessness & chest pain VAS score | X |  | X | X | X |
|  | Daily VAS score completion |  |  |  |  |  |
|  | EQ-5D-5L QoL questionnaire | X |  | X | X | X |
| **Radiological imaging** | Chest x-ray | X | **X** | X | X | X |
|  | Thoracic ultrasound | X | **X** | X | X | X |
|  | CT chest (within preceding 2 weeks) | X |  |  |  | X |
| **Qualitative research** | Participant interviews |  |  |  |  | X |
|  | Focus groups with relatives/carers |  |  |  |  | X |

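### For the minority randomised without an indwelling pleural catheter (IPC), the 14-day wait after insertion uses up nearly all, or all, of the day 0-14 dosing window

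*Protocol*

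**What the plan says.** **Who may be randomised.** Section 6.2 accepts a person with no IPC who is willing to have one and has a suitable effusion. Section 14.1 repeats this and expects most participants to have a catheter already.

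**When the catheter goes in.** The schedule of visits (Section 9.7) marks "Insertion of IPC (if not already in situ" in the Week 0 column. Section 6.4 states: "Random selection will occur at Week 0". Section 8.2.1 is looser: insertion should follow baseline promptly, and no latest day is given.

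**How long to wait.** Section 8.2.1 says: "Participants with a recently inserted IPC should wait at least 14 days before receiving OK432/BCG, if applicable". Section 8.5 likewise advises against placing such devices within 14 days of delivery. Section 6.3 excludes "Recent (<2 weeks) thoracic surgery or invasive pleural intervention", exempting only pleural aspiration, and Section 7.3 has eligibility checked again at the dosing visit. Section 7.2 explains that this exclusion is there to limit infection, whether from BCG or from other bacteria.

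**When to dose.** Section 9.1 gives the intervention arms an extra visit, "one to receive OK432/BCG within 14 days of randomisation (i.e. days 0-14". Section 7.3 sets the same window. Neither makes an exception for a newly inserted catheter.

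**Tolerance.** Section 9.1 adds "Trial visits must occur as scheduled +/- 3 days", "with the exception of the 3 day post intervention visit which must occur on day 3".

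**The concern.** Two clocks run for the same person. One starts at randomisation and closes the dosing window on day 14. The other starts at insertion and does not open dosing until 14 days later. For someone who enters without a catheter, both start on the same day at best. If insertion slips, the second clock opens after the first has closed.

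The site then has three choices: leave the selected person undosed, dose outside the window, or dose before 14 days have passed. The last matters most for the BCG arm, because BCG is a live agent and the interval is the protocol's stated protection against infection. An undosed person still counts in the allocated arm, because Section 13.3 summarises the exploratory secondary outcomes by intention to treat.

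**Working it through.** The protocol gives no calculated figure to reproduce. The check is calendar arithmetic on its stated days.

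**Inputs**
- Random selection: day 0 (Section 6.4).
- Insertion: day *d*. Day 0 as scheduled (Section 9.7); later is allowed (Section 8.2.1).
- Minimum wait from insertion to dosing: 14 days (Section 8.2.1; also Section 8.5, and Section 6.3 through the recheck in Section 7.3).
- Last permitted dosing day *L*: 14 (Sections 7.3 and 9.1), or 14 + 3 = 17 if the tolerance covers dosing.

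**Reference case.** A person whose catheter is at least 14 days old on day 0 has 14 - 0 + 1 = 15 permitted dosing days.

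**New catheter.** Earliest dose = *d* + 14. Permitted days = max(0, *L* - (*d* + 14) + 1).
- With *L* = 14 this is max(0, 1 - *d*).
- With *L* = 17 this is max(0, 4 - *d*).

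| Insertion day | Earliest dose | Permitted days, *L* = 14 | Permitted days, *L* = 17 |
|---|---|---|---|
| 0 | 14 | 1 | 4 |
| 1 | 15 | 0 | 3 |
| 2 | 16 | 0 | 2 |
| 3 | 17 | 0 | 1 |
| 4 | 18 | 0 | 0 |
| 5 or later | 19 or later | 0 | 0 |

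**Does the tolerance cover dosing?** Section 9.1 points both ways. It names the trial visits as weeks 3, 6 and 12 and calls the dosing visit additional, which suggests that the tolerance does not reach dosing. But it exempts only the day-3 safety visit, which is also additional, and that suggests that it does.

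**Effect on the next visits.** Dosing on days 14 to 17 puts the day-3 safety visit on days 17 to 20. The week 3 visit window is 21 - 3 = 18 to 21 + 3 = 24, so the two visits nearly coincide or overlap.

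**The case against.** The best reply is that the rules can be followed as scheduled. Insertion on day 0 and dosing on day 14 satisfy Sections 6.3, 7.3, 8.2.1 and 9.1 together. This stands. A reader might infer that the rules are incompatible for everyone without a catheter. They are not: the zero-day cases need insertion after the Week 0 visit. But Section 8.2.1 allows that, and the scheduled case leaves a single day.

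A reader might also infer that insertion must wait for TILT consent, which Section 5.5 expects a few days after randomisation. The protocol does not say so, and Section 9.7 places insertion before consent.

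The tolerance can fairly be read as covering dosing, since only one of the two additional visits is exempted. That reading eases the problem but does not remove it, because insertion on day 4 or later still leaves no day.

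The wait in Sections 8.2.1 and 8.5 is worded as advice. This also stands, in part. The firm rule is the exclusion in Section 6.3, rechecked at dosing, and it does not name IPC insertion. It does exempt only aspiration, so insertion most naturally falls under it.

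Two larger inferences are not supported:
- The instruction in Section 6.3 to defer treatment after an infection might seem to make this group's position worse. Late deferral can take any participant past day 14, however old the catheter, so it is not evidence on this point.
- A sizeable dilution of the treatment contrast might be inferred. The protocol gives no count of people without a catheter, the efficacy outcomes are exploratory, and Section 13.3 also plans per-protocol and complier average causal effect (CACE) analyses.

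**Conclusion.** The point holds as a minor scheduling conflict. Under the strict window, a person randomised without a catheter has one permitted dosing day if insertion is on day 0, and none if it is later. With the tolerance applied to dosing, insertion on days 0 to 3 leaves 4, 3, 2 or 1 days, and day 4 or later leaves none.

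This assumes that the 14-day wait is observed and, for its binding force, that IPC insertion counts as an invasive pleural intervention under Section 6.3. It concerns only people allocated to OK432 or BCG who enter without a catheter. Section 14.1 implies that this is a minority, but no number is given.

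The three feasibility criteria in Section 9.2 are unaffected. Recruitment counts people randomised, attrition counts withdrawal and loss to follow-up, and an undosed person can still be followed with complete data. Nothing here puts the trial's primary conclusion in doubt.

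**What to change.** Either of two changes to the protocol wording removes the conflict.

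**(a) Tie dosing to insertion for new catheters.** For people whose IPC is inserted at or after Week 0, set the dosing window from the insertion date, for example days 14 to 21 after insertion. State in Section 9.1 whether the 3-day tolerance applies to the dosing visit, and keep the week 3 visit after dosing for these people. Align Sections 7.3, 8.2.1, 9.1 and 9.7.

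The cost is later dosing relative to Week 0 for a few people. With insertion on day 0, dosing on days 14 to 21 leaves 84 - 21 = 63 to 84 - 14 = 70 days to the week 12 visit. The present window leaves 84 - 14 = 70 to 84 - 0 = 84 days. Eligibility and Week 0 do not change.

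**(b) Select later.** Carry out random selection only once the IPC has been in place for 14 days. All 15 dosing days are then available. This also matches how Section 6.3 already treats someone who arrives with a catheter less than 2 weeks old, if insertion counts as an invasive pleural intervention. Sections 6.2, 8.2.1, 9.7 and 14.1 would need to change.

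The cost is larger. Week 0 is delayed by the time to insertion plus 14 days, so at least two weeks, in people required only to have a predicted survival of at least 12 weeks. Baseline tests and CT must be timed to the later Week 0, and some recruitment may be lost.

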### 8.2.2 IPC drainage

IPC drainage will take place in the community, either by district nurses or a trained family member or next of kin. If there are no community resources available to perform drainage, the participant may be drained at their local trial centre.

The drainage regimen will be dictated by clinical need and will be decided by the treating clinician in conjunction with the patient and community team. It is expected that most patients will require drainage approximately 2-3 times per week. Drainage diaries will be kept by all participants.

Participants in the bacterial immunotherapy arms will undergo complete drainage prior to IMP delivery to ensure the drain is patent, and to exclude underlying trapped lung.

### 8.2.3 IPC blockage

All care should be taken to ensure IPCs do not become blocked, beginning with an adequate flush at the end of sclerosant administration. If there is a suspicion that blockage has occurred, perhaps due to cessation of drainage with persistent changes on CXR or TUS, then standard local unblocking procedures should be followed. This may involve a short hospital admission for administration of intrapleural urokinase. Such events should be documented on the appropriate eCRF, on an adverse event form (or SAE form if appropriate) and, as per normal, in the patient’s notes. TSP02 provides a suggested protocol for drain unblocking.

### 8.2.4 Assessment of pleurodesis

Successful pleurodesis is defined as reduction in fluid drainage to ≤50ml on 3 consecutive drainage attempts, with opacification of ≤25% of the ipsilateral hemithorax on CXR. Where there is uncertainty about the presence of fluid on CXR, TUS should be undertaken to assess the volume of residual fluid. If successful pleurodesis is confirmed, the IPC should be removed as soon as possible.

### 8.2.5 IPC removal

Once inserted, drains may be removed at any time at the discretion of the patient’s primary physician, at the request of the patient, or at the discretion of the trial team. Potential reasons for removal include subcutaneous or pleural infection, intolerable pain, significant fluid loculation, or successful pleurodesis. Reason for removal will be documented on eCRFs.

If a drain is to be removed, patients should be given an appointment to have this done within 14 days of the clinical assessment at which this decision was taken. Removal of indwelling pleural catheters should be performed by trained staff under aseptic conditions, and should be followed by a chest x-ray.

Any participant who has their drain removed during their trial period will continue to undergo planned follow-up for the full trial period. Drain removal will be documented on eCRFs.

## Permitted medications

Participants are expected to continue the use of prescribed medications during the course of the study, as identified at baseline assessment, and consistent with study inclusion and exclusion criteria. In addition, all treatments that are considered necessary for a participant’s welfare may be administered at the discretion of the treating clinician or trial investigator in keeping with standard medical practice.

Participants in both arms will receive best supportive care alongside the investigational products, with the exception of oral steroids, which should be avoided, if possible, in the 14 days before and after OK432/BCG delivery. Analgesia, anti-emetics and antipyretics can be given as required, in accordance with local prescribing guidelines.

The following medications will be delivered to all participants who receive OK-423 or BCG, as stated in the trial manual:

- Up to 200mg 1% Lignocaine administered intra-pleurally contemporaneously with OK432/BCG delivery.
- Paracetamol, oral or intra-venous to a maximum dose of 4g per 24 hours, delivered immediately prior to OK432/BCG delivery and as required subsequently
- Opioid analgesia, including oral codeine phosphate 30-60mg to a maximum of 240mg in 24 hours, or oral morphine sulphate at a dose that is appropriate to the participant’s current and previous use of morphine, delivered immediately prior to OK432/BCG delivery and as required subsequently
- Medications to treat any treatment-emergent AEs

Medications to treat treatment-emergent AEs should not interfere with the study and can be used at the investigator’s discretion. Antipyretics and anti-inflammatories may be used to treat fever or to prevent recurrence of fever.

Subjects with clinical symptoms or signs of infection should have a clinically relevant evaluation, including appropriate bacterial cultures. If pleural infection is suspected, a sample of pleural fluid should be taken and sent for biochemical and microbiogical assessment. If antibiotics are required, in the opinion of the treating clinician, local guidance should be followed, to include gram positive and anaerobic cover. The preferred regimen would include either co-amoxiclav or Tazocin. The decision regarding intra-venous or oral treatment should be made by the treating clinician.

Participants in the control arm are permitted to receive chemotherapy or immunotherapy at the discretion of the treating clinician. Wherever possible, however, the commencement of disease-modifying treatments should be delayed until the end of the 12 week TILT trial period.

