## Intervention visit

Participants who are randomised to bacterial immunotherapy will be invited to receive a single administration of OK432 or BCG, depending on which arm they are allocated to. The dose of OK432 is 10KE and the dose of BCG is 0.4-1.6x10^7^ CFU.. However, reduced dose options (5KE of OK432 and 0.2-0.8 x 10^7^ CFU of BCG) can be used (based on the discretion of the treating clinician) in older patients, those with higher performance status, people with multiple medical co-morbidities, or those at higher risk of experiencing or not coping with an adverse event. The immunotherapy agent will be delivered intra-pleurally via an indwelling pleural catheter within 14 days of random selection (i.e. days 0-14).

For the intervention visit, participants will attend hospital and undergo medical assessment to ensure they remain eligible and suitable to receive OK432/BCG. This will include complete drainage of the effusion, to ensure IPC patency, followed by a CXR to exclude trapped lung. If they remain eligible, up to 3mg/kg of 1% lignocaine (to a maximum of 250mg) will be instilled intra-pleurally followed by the appropriate agent, in adherence with the Trial Specific Protocol 4 (TSP 04). The IPC will then be disconnected and OK432/BCG left within the pleural cavity for 1 hour. After 1 hour, further drainage will be undertaken and the participant will be observed for another hour before returning home.

Following the intervention, patients will be advised to take regular prophylactic paracetamol and ibuprofen for the subsequent 3 days to reduce the risk of fevers, sweats and pain.

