## Non-permitted medications

The following therapies are not permitted during TILT:

- Any chemotherapy or immunotherapy (participants who receive the intervention only)
- Granulocyte colony stimulating factor (GCSF) or Granulocyte macrophage colony-stimulating factor
- Other known immunosuppressive or immunomodulatory medication

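### Section 8.3 only discourages oral steroids around delivery, while 6.3 and 8.4 bar immunosuppressive medication, so the rules on giving live BCG to a steroid user conflict

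*Protocol*

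**What the plan says.** Four sections of the protocol bear on this.

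- **6.3 Exclusion criteria.** A participant must have none of the listed criteria. One of them is "Known immunodeficiency or immuno-suppressive medication", with no dose, route or steroid exception. The infection criterion in the same list carries a deferral instruction ("treatment should be deferred for 7-14 days"); the immunosuppression criterion does not.
- **7.3 Intervention visit.** Before the agent is given, participants "undergo medical assessment to ensure they remain eligible and suitable to receive OK432/BCG". Delivery must fall on day 0-14 after random selection.
- **8.3 Permitted medications.** Existing prescriptions may continue "as identified at baseline assessment, and consistent with study inclusion and exclusion criteria". Treatments needed for the participant's welfare "may be administered at the discretion of the treating clinician or trial investigator in keeping with standard medical practice". Supportive care is given with the exception of "oral steroids, which should be avoided, if possible, in the 14 days before and after OK432/BCG delivery". The same wording covers both agents.
- **8.4 Non-permitted medications.** Among the therapies not permitted during TILT is "Other known immunosuppressive or immunomodulatory medication". There is no exception and no reference back to 8.3.

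No section says whether oral steroids are immunosuppressive medication for these purposes, or which section prevails.

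**The concern.** The practical decision is whether to put a live organism into the pleural space of someone taking oral steroids. Section 7.2 describes BCG as live attenuated. Section 14.3 treats disseminated BCG infection as rare but important. Section 7.2 also rules out isoniazid prophylaxis, and it relies on an exclusion criterion (recent surgery or pleural intervention) to limit infection risk. Eligibility is therefore one of the main safeguards, and for steroids it is unclear.

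The trial runs at three hospitals (6.1). One investigator could cite 6.3 and 7.3 and refuse to dose. Another could cite 8.3, judge that steroids could not be avoided, and go ahead. Both would believe they were following the protocol. After delivery, one section discourages steroids for a fortnight and another prohibits immunosuppressive drugs, so it is unclear whether a steroid course in that period is a protocol deviation.

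OK432 is inactivated (Plain English summary), so the concern lies mainly with the BCG arm.

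**Working it through.** The protocol gives no figure to reproduce here. The check sets the rules side by side, then tests whether a firm rule would fit the delivery window.

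**Premise.** Systemic oral steroids at immunosuppressive doses count as immunosuppressive medication. This is general clinical knowledge, not protocol text, and it depends on dose.

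**Before delivery**

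- Under 6.3 with 7.3, a participant on such a dose at the intervention visit is no longer eligible and is not dosed.
- Under 8.3, steroids in the preceding 14 days are to be avoided where possible. The qualifier accepts that some participants will have taken them, and the section attaches no consequence for dosing.
- The periods overlap. With delivery on day d, where d is 0 to 14, the 14 days before it begin on day d − 14, that is, between day −14 and day 0. The soft rule therefore always reaches back to the screening and randomisation visit or earlier, and runs up to the recheck. It covers the period in which 6.3 is assessed and reassessed.
- Section 8.4 adds little here. It applies during TILT, and section 6.5 (Consent) starts TILT participation at signed TILT consent, which the schedule of visits places at the intervention visit. The pre-dose conflict therefore rests mainly on 6.3 and 7.3 against 8.3.

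**After delivery**

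- 8.3 discourages oral steroids for 14 days and sets no specific limit on them afterwards.
- 8.3 also permits treatment needed for welfare at clinical discretion.
- 8.4 prohibits immunosuppressive medication during TILT without exception.
- The three statements do not give one answer.

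**Does a firm 14-day rule fit the window?** Let L be the day of the last oral steroid dose, and require d − L ≥ 14 with 0 ≤ d ≤ 14. The latest permitted d is 14, so L ≤ 14 − 14 = 0.

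- L ≤ −14: no deferral is needed (−14 + 14 = 0).
- L = −13: earliest d = −13 + 14 = 1. L = 0: earliest d = 0 + 14 = 14. Deferral fits the window.
- L = 1: earliest d = 15. L = 14: earliest d = 28. Both are outside the window, so the agent would be withheld.

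This arithmetic describes how the proposed rule would work. It does not measure how often the problem will occur.

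**Size.** The flowchart plans 4 participants for BCG. Withholding from one leaves at most 4 − 1 = 3 of 4 treated.

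**The case against.** The strongest reply is that the sections can be read together. Section 8.3 guides supportive care: it tells clinicians what to avoid prescribing. It does not say that someone who took steroids may be dosed. That decision belongs to 7.3, which requires the participant to be both eligible and suitable, and 6.3 ends with a discretionary exclusion for the Chief Investigator. Section 8.3 itself limits continued medication to what fits the eligibility criteria. There is also monitoring for disseminated BCG at every trial visit (14.3), and the administration procedure (TSP 04), which is not shown, may address steroids.

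Much of this stands. A reader might infer that 8.3 authorises BCG under steroids; it does not say so. A reader might also take 8.4 as a ban without time limit; it is confined to TILT. And a reader might treat any oral steroid at any dose as barred by 6.3; the protocol does not define the term, and a replacement dose need not be immunosuppressive.

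The reply does not remove the conflict at immunosuppressive doses. If 6.3 and 7.3 stop dosing in that case, a request to avoid steroids only where possible before delivery has no clear function for those doses. If 8.3 is instead the specific rule for steroids, it is an exception that neither 6.3 nor 8.4 acknowledges. The consistency clause in 8.3 does not help, because nothing says whether steroids fall under the criteria it points to. Discretion and monitoring reduce the consequences but do not supply a common rule.

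**Conclusion.** The point holds for oral steroids at immunosuppressive doses. Before delivery, 6.3 with 7.3 conflicts with 8.3 on whether such a participant may receive BCG. After delivery, 8.3 and 8.4 do not agree on whether steroids may be used. A stated soft rule meets stated hard rules on a patient-safety decision, so this is more than missing detail and should be corrected.

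The conclusion rests on the dose-dependent premise that these steroids are immunosuppressive. The exposed group is small: mainly the 4 participants planned for BCG.

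A reader might infer that the defect threatens the feasibility targets or the analysis. The documents do not support that. They give no rate of steroid use, so no frequency can be stated. Outcomes are summarised as randomised (13.3), and no statistical figure changes. Nor do the documents support an equally firm bar for OK432, which is inactivated.

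**What to change.** - **6.3 and 8.4.** State that immunosuppressive medication includes systemic oral steroids above physiological replacement dose.
- **8.3, BCG arm.** Replace the qualified request with a firm rule: do not give BCG if such steroids were taken in the preceding 14 days. Defer if delivery can still fall on day 0-14; otherwise withhold and follow up as randomised.
- **8.3, OK432 arm.** The softer wording may stay if the sponsor wishes, provided it is written as an explicit exception to 6.3 and 8.4.
- **After delivery.** Make 8.3 and 8.4 say the same thing: such steroids are not permitted unless clinically necessary, and any use is recorded on the eCRF.

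The cost is a few words in three sections. No new data are needed: medication history is already taken at the screening and intervention visits (9.7), and all concomitant medication is already recorded on eCRFs (8.7). The downside is that an occasional steroid user in the 4-person BCG arm is deferred or not dosed.
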